### Study purpose and specific aims

The primary goal of this study is to evaluate the efficacy of a pain self-management group intervention (SMG), as compared with a control condition (BOOK), in decreasing physical disability, pain, pain-related interference with activities, and depression in older retirement community residents with chronic pain. In addition, we wish to determine the extent to which SMG participation is associated with changes in specific pain-related beliefs and coping strategies, and the extent to which changes in these process variables are associated with changes in outcomes (physical disability, pain intensity, pain-related interference with activities, and depression). We plan to test the following hypotheses:

*1. *At post-treatment and each follow-up, participants assigned to SMG, as compared with participants assigned to BOOK, will report less physical disability (primary outcome), and lower pain intensity, pain-related interference with activities, and depressive symptom severity (secondary outcomes).

*2. *Participants assigned to SMG, as compared with participants assigned to BOOK, will show greater pre- to post-treatment increases in self-efficacy and use of adaptive pain coping strategies and greater decreases in catastrophizing. Significant differences between SMG and BOOK groups in pain-related beliefs and coping strategies will be maintained at 6-month and 1-year follow-ups.

*3. *Pre- to post-treatment changes in specific pain-related beliefs (catastrophizing, self-efficacy) and coping strategies (Chronic Pain Coping Inventory subscales) will be associated significantly with changes in physical and social functioning, pain intensity, and depression over the same period among SMG participants. These changes in beliefs and coping strategies will be maintained at 6-month and 1-year follow-ups.

Figure 1 depicts the hypothesized relationships among study variables.

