### Measures

Study measures were chosen based on psychometric properties, including sensitivity to change; brevity; and appropriateness for use with community-dwelling, older adults with chronic pain. They are described below and summarized in Table 2.

**Table 2 T2:** Measures and assessment times

**CONSTRUCT/MEASURE**	**SCREENING/BASELINE**	**POST-INTERVENTION**	**6-MONTH FOLLOW-UP**	**12-MONTH FOLLOW-UP**
**Physical Functioning**	√	√	√	√
Roland-Morris Disability Questionnaire				
Brief Pain Inventory (BPI) – pain interference subscale				
**Pain Intensity**	√	√	√	√
Brief Pain Inventory – pain intensity subscale				
**Mood Disturbance/ Social functioning**	√	√		√
Geriatric Depression Scale				
**Pain Beliefs and Coping**	√	√		√
Chronic Pain Coping Inventory – (*includes pain medication use)*				
Coping Strategies Questionnaire – catastrophizing, praying/hoping subscales				
Self-efficacy Scale				
**Pain Knowledge**	√	√		
**Demographics, Medical Conditions, Medications**	√			
Screening & Intake Questionnaire				
Adapted Charlson Index				
**Cognitive Functioning**	√			
Folstein Mini-Mental State Examination				
**Pretreatment Expectations**	√			
**Adherence to Treatment**		√		√
Attendance at classes				
Completion of reading assignments				
Attainment of goals (Personal Pain Management Plan)				

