##### Chronic pain coping inventory (CPCI)

The CPCI measures cognitive and behavioral coping strategies used by people to manage chronic pain. It contains 9 subscales: guarding, resting, asking for assistance, relaxation, task persistence, exercise/stretch, seeking support, coping self-statements, and medication use [47]. The CPCI scales have been shown to have acceptable internal consistency and test-retest reliability, and to be associated significantly with physical disability and depression [47-49]. Additional development and psychometric testing have supported the reliability and validity of an additional activity pacing subscale [49].

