#### Statistical analysis

The test of hypothesis 1 compares the SMG and BOOK participants on the primary outcome (physical disability) and secondary outcomes (pain intensity, pain-related interference with activities, and depressive symptom severity) at each of the 3 follow-up assessments. The analytic method that we will use to evaluate this hypothesis is the mixed effects analysis of covariance (ANCOVA), as proposed by Laird and Ware [64] and implemented in the SAS PROC MIXED procedure [65,66]. This model will have two random effects, *site *and *person nested within site*. *Group *(i.e., treatment or control) and *Time *will be fixed effects. The repeated measurements of physical disability at post-intervention, 6 months, and 1 year will be the outcome measure. The baseline value of physical disability will be included in the model as a covariate. Any baseline variables that are correlated with the outcome variable and/or differ between the two treatment groups (e.g., gender, age, comorbidity) will also be included as covariates in the analysis. If the main effect for *group *is significant, contrasts within this model will be used to test for treatment effect separately at each of the three outcome times. Secondary analyses will be similar, fitting a mixed effects model that uses one of the secondary outcomes (e.g., pain intensity, pain-related interference, and depression) in place of physical disability. The analysis of Hypothesis 1 will be by intent-to-treat.

Hypothesis 2 involves comparing the SMG and BOOK groups on changes in process variables (pain-related beliefs and coping strategies). A mixed effects model, as described under hypothesis 1, will be used for these analyses. As for hypothesis 1, baseline variables that are predictive of outcome and/or differ between groups will be included as covariates in the analyses for hypothesis 2.

Hypothesis 3 involves the correlation of changes in beliefs and coping to changes in the outcome variables. For each assessment time, change from baseline will be computed and scatter plots will be used to describe relationships, with Pearson and/or Spearman correlation coefficients used to summarize the strength of the association. Although we hypothesize that significant associations in changes will occur only in the SMG group, we also will perform exploratory analyses in the BOOK group to assess for these associations.

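### Hypothesis 3 expects process–outcome associations only in SMG, but the stated within-arm correlations include no test of whether the arms differ

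*Protocol article*

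**What the plan says.** Under Study purpose and specific aims, Hypothesis 3 is a statement about one arm. Pre- to post-treatment changes in beliefs and coping "will be associated significantly with changes in physical and social functioning, pain intensity, and depression over the same period among SMG participants".

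The Statistical analysis section gives the method: "For each assessment time, change from baseline will be computed and scatter plots will be used to describe relationships". How strong each association is will be summarised by a Pearson coefficient, a Spearman coefficient or both. The section then adds an expectation that involves both arms: "Although we hypothesize that significant associations in changes will occur only in the SMG group, we also will perform exploratory analyses in the BOOK group".

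Neither section gives a process-by-group interaction or a test of the difference between two correlations for this hypothesis. The other analyses in the same section are built differently. Hypotheses 1 and 2 use a mixed model with a site effect and baseline covariates, and the exploratory subgroup analyses are given an explicit interaction with treatment group.

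**The concern.** That an association is present in SMG only is a claim about the difference between SMG and BOOK. Computing a correlation in each arm and seeing which one passes a significance threshold does not test that difference. One arm can pass and the other fail through sampling variation alone, even when the true association is identical.

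At stake is the interpretation of mechanism. An SMG-only pattern would invite the reading that changes in beliefs and coping drive outcome in the programme and not under the book control. As the analysis is stated, nothing separates that reading from chance discordance between two samples of the same size.

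**Working it through.** **The plan's own figures.** No figure is stated for Hypothesis 3, so the check starts from the sample-size section.
- Completers: 273 × 0.8 = 218.4, matching the stated 218.
- Effective sample size at ICC 0.1: 218 / (1 + (6.41 − 1) × 0.1) = 141.5, against 141 in Table 3.
- Power for effect size 0.5: 84.5% by the normal approximation and 84.0% by the t distribution, against the stated 84%. These reproduce.

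**Inputs for Hypothesis 3.**
- About 109 completers per arm: 218 / 2, assuming an equal split because the sites are split 17:17.
- Two-sided 5% level: assumed, as the article states none.
- The same true correlation r in both arms: assumed and varied, since the article gives no expected value.

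**Chance of a spurious SMG-only pattern.** By Fisher's z, the standard error in one arm is 1/√(109 − 3) = 0.0971. Within-arm power p is the probability that atanh(r)/0.0971 plus a standard normal error falls beyond ±1.96. The arms are independent, so the probability of a significant result in SMG and a non-significant one in BOOK is p × (1 − p).

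Example at r = 0.20: atanh(0.20) = 0.2027, and 0.2027/0.0971 = 2.09. Then p = 0.551, and 0.551 × 0.449 = 0.247.

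| True r in both arms | Power p per arm | SMG-only pattern, p(1 − p) |
|---|---|---|
| 0 | 0.050 | 4.8% |
| 0.10 | 0.178 | 14.7% |
| 0.15 | 0.343 | 22.5% |
| 0.20 | 0.551 | 24.7% |
| 0.25 | 0.748 | 18.8% |
| 0.30 | 0.890 | 9.8% |
| 0.40 | 0.992 | 0.8% |

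The product p(1 − p) cannot exceed 25%, which it reaches when power is 50%. A direct test of the difference gives 5% in every row.

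**Sensitivity to n.** The 109 applies at 12 months, and more participants may have data after treatment. With 136 per arm (about 273 / 2, no attrition) the pattern occurs with probability 16.7% at r = 0.10, 24.3% at 0.15, 22.8% at 0.20, 13.6% at 0.25, 5.1% at 0.30 and 0.2% at 0.40. The range of r at risk shifts down slightly; the peak stays just under 25%.

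**What a direct test can detect.** The standard error of the difference between two Fisher z values is √(2/106) = 0.137. For 0.3 against 0: 0.3095/0.137 = 2.25, giving power of about 62%. Power is 33% for 0.3 against 0.1, 65% for 0.4 against 0.1, and 87% for 0.4 against 0. With BOOK at 0, 80% power needs an SMG correlation of about 0.37, since (1.96 + 0.84) × 0.137 = 0.385 on the z scale.

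**Number of pairs, as context.** The hypothesis names "specific pain-related beliefs (catastrophizing, self-efficacy) and coping strategies (Chronic Pain Coping Inventory subscales"), and the CPCI description lists 9 subscales. That makes 2 + 9 = 11 process variables, or 12 with activity pacing. The aims list four outcomes. The pre-post hypothesis therefore covers 11 × 4 = 44 to 12 × 4 = 48 pairs in SMG. Table 2 marks the "Pain Beliefs and Coping" measures at two times after baseline (post-intervention and 12 months), so including 12 months gives 88 to 96.

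**The case against.** The strongest defence is that the article never states a rule for concluding that an association exists only in SMG. Formal Hypothesis 3 is confined to SMG participants, the coefficients are described as summaries of strength, and the BOOK work is labelled exploratory. This stands: a reader might infer that the authors will draw the SMG-only conclusion from separate tests, but the article does not say so. It remains that the Statistical analysis section states a between-arm expectation and offers no analysis able to address it.

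Second, 25% is the ceiling of p(1 − p), not a typical value. This also stands. At r = 0 the pattern is no more frequent than the error of a direct test, and at r = 0.40 it is rarer. The exposure lies at modest correlations, and the article does not say what correlations it expects.

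Third, three stronger readings are tempting and are not supported:
- *About 90 uncorrected tests as an error in itself.* The formal pre-post hypothesis has 44 to 48 pairs. A multiplicity rule for a non-primary analysis, like the choice between Pearson and Spearman, may be left to the full analysis plan.
- *Correlations badly distorted by ignoring site.* The variance inflation of a person-level correlation follows the product of the two ICCs. With 0.1 for both (assumed for the process scale), it is 1 + 5.4 × 0.1 × 0.1, about 1.05. A simulation of 17 sites of 6 people with no true association rejected 5.7% of the time at ICC 0.10.
- *Hypothesis 3 as the trial's whole evidence on mechanism.* Hypothesis 2 is the randomised comparison of the process variables and has a suitable mixed model.

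**Conclusion.** The point holds in a limited form. The article hypothesises associations in SMG only and pairs this with separate within-arm correlations, so an SMG-only statement would have no valid stated basis. For a given pair with equal true correlations in the two arms, the misleading pattern occurs about 15% to 25% of the time for r between 0.10 and 0.25, about 10% at 0.30 and 1% at 0.40, against 5% for a direct test. These figures assume 109 completers per arm, a two-sided 5% level and negligible clustering of the correlation. The consequence is confined to the interpretation of mechanism; the primary outcome, the sample size and Hypotheses 1 and 2 are untouched.

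**What to change.** For each process–outcome pair, add process change, group and their interaction to the mixed model with site effect and baseline covariates already planned for Hypotheses 1 and 2. Base any statement that an association is specific to SMG on the interaction term alone. Keep the scatter plots and correlation coefficients as description.

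If the investigators do not want that analysis, the alternative is to drop *only* from the Statistical analysis section and label Hypothesis 3 descriptive.

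No new data are needed, only some extra modelling. The cost is power: by the two-correlation approximation, about 62% for 0.3 against 0 and 33% for 0.3 against 0.1. Fewer SMG-only statements will stand, and a non-significant interaction should not be read as showing that the arms are alike.

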## Discussion

Persistent pain is a common problem in older adults that can be debilitating. Self-management strategies that incorporate physical and psychosocial pain coping skills are effective in decreasing pain and improving function and mood in younger adults. Little is known, however, about the efficacy of this therapy for older adults, especially those in the mid-old to old-old range. Our randomized controlled trial assesses the efficacy of such a treatment program, as compared with a control condition, in decreasing pain and improving physical and psychosocial functioning in elderly retirement community residents with chronic pain.
